## Trial Design {8}

This multi-site single-blind randomised controlled trial (RCT) compares two services, IPS and SAU. The study will be a parallel, two-arm pilot RCT with a 1:1 allocation ratio across the two trial arms [1]. We will utilise a pre-post and 3/6-month follow-up design with embedded mixed-method process evaluation and exploratory economic analysis.

## Methods: Participants, Interventions and Outcomes

### Study Setting {9}

The study settings are social care services in the local authorities feeding into the two trial sites: Glasgow City Council (Scotland) and the London Borough of Bromley (England). Although each site is in the UK, the social services and legal contexts in each differ considerably. With regards to levels of deprivation, Bromley is a relatively small borough and relatively prosperous. Nonetheless, there are pockets of deprivation particularly in the North-East and North-West of the borough [77]. Glasgow City council is one of the largest local authorities in the UK. Although it does cover prosperous areas there are extensive areas of multiple deprivation [78].

### Eligibility Criteria {10}

#### Inclusion

At this early stage we have employed a broad eligibility criterion. Our target population is ‘children in need’ (or the Scottish equivalent); that is, “*a child who is unlikely to reach or maintain a satisfactory level of health or development, or their health or development will be significantly impaired without the provision of children’s social care services*” (p. 53) [79]. Eligible participants are families in the Glasgow or London trial sites where i) the infant(s) are aged 0–5 years (having additional children aged above 5 will not exclude the family from participating), ii) the family has an allocated social worker and plus a multi-agency support plan. The latter may include but is not limited to child and adolescent mental health services, paediatrics, or educational psychology, and where an infant and/or parent has a mental health problem or neurodevelopmental condition. Screening measures will be used to recruit families whose infants demonstrate some mental health and family relationships problems.

#### Exclusion

IPS is an early intervention and the families who are likely to benefit from it are those whose problems are severe enough that IPS will offer tangible benefits, yet whose problems are not so entrenched that change is impossible. Therefore, potential participants will be excluded from the study if the infant has a Child Protection Plan (CPP) or is on the Child Protection Register (CPR), the family are in the process of ‘stepping down’ from a CPP or CPR, or if the infant is currently engaged in therapeutic work. For parent participants who are currently accessing addiction and/or mental health services, cases will be examined on an individual basis by the Recruitment Co-ordinator (RC; see Recruitment below). For instance, following a discussion with the recovery workers supporting the parent, the research team assessment regarding inclusion would be made based on the parent’s capacity to engage with therapeutic support and if this was viable alongside their existing recovery plan and treatment. The flow of participants through the study is shown in Fig. 2.

**Fig. 2 Fig2:**
[figure not shown]
SPIRIT flow diagram of participants through the trial

## Interventions

### Intervention Description {11a}: Infant and Family Support (IPS)

The experimental intervention is IPS, which aims to improve infant-parent relationships and reduce the risk of children needing to come into care for families who have a social worker. IPS is delivered by multi-disciplinary infant mental health teams operating to the NSPCC’s (National Society for the Prevention of Cruelty to Children) safeguarding and equality and diversity policies, with local authorities retaining ultimate safeguarding responsibility subject to English [79, 80] requirements. Within IPS, Family Engagement Workers (FEWs; discussed further below) have expertise-by-experience of having a child in need, other IPS practitioners have expertise-by-training and working in social work, psychology, or psychiatry, and some have both types of expertise.

IPS is derived from the New Orleans Intervention Model (NIM) [26] and has been extensively used by IFT teams [28]. As such, IPS professionals are already trained in the infant mental health assessment and interventions that will be used, although supplementary training was provided around poverty awareness and neurodevelopmental conditions. In addition, the co-production of IPS has led to adaptations to NIM, with the most significant changes being the addition of the Social Needs Questionnaire (SNQ) and ESSENCE-D [81] during the formulation phase. The SNQ assesses families’ personal, social, and financial needs, allowing the identification of supports required, as well as facilitating access to these supports as part of the intervention. Essence-D is a new tool designed to help practitioners to support families to develop a better understanding of either their child’s or their own neurodevelopmental profile. The information collected will be included in the formulation, and the intervention offered will be modified according to any neurodiversity needs identified.

Like the IFTs already operating in Glasgow and London, the IPS teams will use evidence-based relationship-focused interventions (up to 4 months) of the kind shown to reduce child abuse risk/increase parental sensitivity [82, 83]. This will ensure families receive a bespoke relationship-focused intervention that aims to be tailored to their unique needs. As the inclusion of FEWs to the IPS team is a new development (see below), there will be time allocated to induction and team building at the start. The family’s exit from IPS involves a “warm handover” to other local community services.

Using a poverty-aware and relationship-focused approach, the intervention will aim to improve infant mental health via improvements in the family’s material circumstances and infant-parent relationships – with the ultimate aim of the infant safely remaining within their birth family. Should child protection proceedings be required, learning about relationship quality and the degree of change achieved through intervention, will inform recommendations to the social care system.

#### Family Engagement Works and Family Engagement Leads

Our early co-production work highlighted the need for a Lived Experience workforce to help bridge the gap between IPS and the families that will use the service. As a result, the IPS teams will include two Family Engagement Workers (FEW) and a Family Engagement Lead. The Family Engagement Worker, informed by their own experiences of working with services, will work alongside families as they are randomised into IPS, discussing the intervention, seeking informed consent, arranging appointments (which could include preference for home visit or office appointments, transport/childcare needs, and identifying any learning, language, or cultural needs) and conducting some of the early assessments with families. In particular, the FEW will enhance the relationships between professionals (e.g., social workers and clinicians) and families through working with parents and caregivers, to promote choice and opportunities to enable families to feel connected and valued in their assessment and support plan. Family engagement is tailored to meet the local needs of families and support their connections with other helpful networks and services.

The Family Engagement Lead will ensure FEWs are fully supported to deliver safe, quality interventions with families within the wider team, and ensuring that decisions and practices are informed by lived experience at all levels. Their role will be to recognise and consciously work to remove barriers for the Lived Experience workforce, including practical constraints, attitudes/workplace culture, and bureaucratic processes that restrict effective and authentic Lived Experience work. Following the development phase establishing the need and readiness for this feasibility trial, this paper now outlines the protocol for the feasibility trial of IPS.

### Services as Usual {6b}

Families not randomised to IPS will receive services as usual (SAU), i.e., any assessment and/or support that social services and others normally implement when children have an allocated social worker. SAU includes regular contact with families by a social worker Case Manager, and may include signposting of families towards existing Health and/or third sector services depending on needs and availability of services. Families receiving IPS will continue to receive SAU in addition to IPS unless they were case closures to children services.

Services-as-usual (SAU) are often complex, involving health, social care and third sector services. In BeST^?^ [26] and our earlier work in this study [62] we created detailed maps of these local services, and have supported multi-agency partnerships between these services, in Glasgow and Bromley. Families’ journeys through SAU will be monitored, both qualitatively via continued systems mapping, and quantitatively via participant-level service use data also feeding into economic evaluation.

### Outcomes {12}

The primary outcome will be the success of recruitment and retention of 30 families.

The secondary outcomes are:Acceptability and feasibility of planned outcome measures for a definitive RCT (see below), including the newly developed parent-reported outcome measure (PROM) and parent-reported experience measures (PREM; see later)Acceptability of the IPS intervention to both families and professionalsPerceived changes in the organisation, access, and quality of services, for children with a Social WorkerFeasibility and acceptability of bespoke service use questionnaires, data collection forms and health related quality of life (HRQoL) measures to inform the future cost-effectiveness of IPS versus SAU.

#### Primary Outcome Measure

Our primary outcome measures will capture the following elements (Table 1):Can we identify and randomise 30 eligible families across Glasgow and Bromley? *This will capture the proportion of eligible families that consented to the trial, as well as qualitative data on recruitment procedures and pathways.*Can a sufficient proportion of these 30 families be retained in the study for 3 and/or 6 months post randomisation? *Quantitative data will include proportions of families retained in the trial, and qualitative data will focus on reasons for attrition.*

We will also collect data on any ambiguities regarding eligibility criteria, reasons for ineligibility and non-participation, to inform the design and conduct of a definitive trial.

#### Secondary Outcome Measures

Our secondary outcomes will focus on the acceptability and feasibility of both the proposed evaluation methodology and the intervention itself. This will predominantly be examined through a detailed process evaluation (see below), although quantitative data regarding assessment completion rates, errors, and missing data, as well as the differential impact of face to face and remote assessments will also support our analysis.

#### Putative Outcome Measures for Definitive Trial

The following outcome measures have been selected with the aim of addressing the key components of our IPS logic model (Fig. 3) and will be administered to all families at pre-randomisation and 3-to-6 months follow up to determine the feasibility and acceptability of their inclusion for a definitive trial. These measures have been selected through our review of the literature and some are being used in ongoing RCTs in similar populations [26] (Table 2).

**Fig. 3 Fig3:**
[figure not shown]
The logic model, IPS, *[name] and [name] [84]

**Table 2 Tab2:** Study Procedures

**Activity / Assessment**	Staff Member	Initial Referral	Prestudy screening/consent	Prestudy Baseline assessment	Randomisation	Follow-up 3/6 months postbaseline
Eligibility Assessment	SW	✔				
Participant Information Sheet	RC		✔			
Consent^1^	RC		✔			
Privacy Notice	RC		✔			
Randomisation	TM				✔	
***Infant-based measures***						
b-CAPI * To be completed for all children*	RN			✔		✔
SDQ * To be completed for children aged 2 and over, according to age of child:* * ◦ 2-4y, 4-17y*	RN			✔		✔
ITSEA * To be completed for children aged 2 and under*	RN			✔		✔
PEDs-QL * To be completed for all children, according to age of child:* * ◦ 1–12 m, 13–24 m, 2-4y, 5-7y*	RN			✔		✔
***Parent-based measures***				✔		✔
Demographic and Service Use Questionnaire	RN			✔		✔
GHQ-12	RN			✔		✔
ICECAP-A	RN			✔		✔
PREM	RA/FEW			✔		✔
PROM	RA/FEW			✔		✔
Parent Qualitative interview	RA			✔		✔
***Professional-based measures***						
Professional Focus group Parent Collaborator Focus group / interview	RA RA					✔ (+ as required) ✔ (+ as required)

Key: ^1^Consent will take place a minimum of 24 h after information has been presented to families

*SW* Social worker, *RC* recruitment co-ordinator, *TM* trial manager, *RN* research nurse, *RA* research associate, *FEW* family engagement worker, *b-CAP* Brief Child Abuse Potential Inventory, b-CAP, *SDQ* Strengths and Difficulties Questionnaire, *ITSEA* Infant–Toddler Social & Emotional Assessment, *PEDs-QL* Paediatric Quality of Life Inventory, *GHQ-12* General Health Questionnaire, *ICECAP-A* ICEpop CAPability measure for Adults, *PROM* parent-reported outcome measure, *PREM* parent-reported experience measure

##### Infant Mental Health

In a definitive trial our primary outcome will be infant mental health and our planned principal outcome measure will be the Brief Child Abuse Potential Inventory (b-CAP; [85]). This is a parent-report instrument that measures risk of child maltreatment. Secondary outcomes will be the Paediatric Quality of Life Inventory (PedsQL [86]), which assesses health-related quality of life and, depending upon the child’s age, either the Strengths and Difficulties Questionnaire (SDQ [87]) or the Infant–Toddler Socio-emotional Assessment (ITSEA [88]) to characterise children's Social–Emotional Development (Table 2).

##### Parental Mental Health

Parent mental health will be captured though the General Health Questionnaire (GHQ-12 [89]) which is a well validated measure of nonspecific psychological distress. In addition, the ICEpop CAPability measure for Adults (ICECAP-A, [90]) will be assessed and can be used to calculate parent utilities in the economic analysis. The ICECAP captures attributes of wellbeing which are important to adults so has a broader definition of QoL than the GHQ which focusses on health.

##### Parent-Reported Outcome Measure and Parent-Reported Experience Measure

In addition to the validated outcome measures described above, an important output of our earlier co-production and qualitative process evaluation work was the development of a parent-reported outcome measure (PROM) and parent-reported experience measure (PREM) to capture outcomes and experiences that are salient to our families when engaging with social care. These measures will be piloted with families in the current study and completed with the researcher and lived experience lead.

PROMs have been successfully used in healthcare to inform shared decision-making and to tailor care to individual needs, and are increasingly used in randomised controlled trials to examine whether an intervention is effective and cost-effective from the perspective of service-users [91]. PREMS are used to examine patients’ experiences of healthcare and examine factors such as empathy and respect [92]. Although the role of PROMs and PREMs in health care is increasingly being recognised, to our knowledge this will be the first time PROMS and PREMS have been developed for a social care context. In line with the theoretical basis for this study that highlights how stigma, shame, and structural inequalities are key problem drivers, and that respect, reduction in shame, and development of trust are crucial in allowing relationship-focused interventions to be effective, we believe that development of these new tools will be essential. The data from the PROM and PREM will also feed into the economic evaluation (see below).

#### Data Capture on Resource Use for Service/Intervention Delivery for IPS/SAU

In a future trial we will undertake a full economic evaluation and decision analytic model, exploring the potential cost-effectiveness of IPS in comparison to SAU. Currently, we will test our planned health economic methods for use in definitive evaluations, including the feasibility of collecting data on (i) intervention delivery in IPS and SAU, (ii) self-reported service use, and (ii) quality-of-life measures. To examine resource use associated with IPS, as well other service impacts, we will generate data from NSPCC system routine data (e.g. data on number of meetings, attendees, duration, training, and other costs) to calculate a unit and total costs for future trials. In a future definitive study, we would explore linkage with routine NHS data to allow validation of participant-report data to allow a full economic model to be constructed. In order to get resource use information for the SAU arm, a data collection form was adapted from a previously developed form for the BeST^?^ Trial [26]. Measurement of quality of life is an important outcome for the economic component of this study and will enable exploration of potential short-term changes in quality of life for children between baseline and 3-6 months, and between the trial arms. The ICECAP-A will also be used to inform the economic evaluation, deriving utility values for the parents.

##### Demographics and Service use Questionnaire

Based on prior experience from the BeST^?^ Trial [26], we anticipate potential challenges in obtaining resource use data from services as usual. Therefore, we plan to additionally capture parent reported use of services in each arm as an alternative data source. This will document use of health, education, and social care service use both within IPS and SAU, as well as the parent(s) demographics and circumstances such as employment, benefits, and housing. This will be collected at baseline and follow up (3-6 months).

### Process Evaluation

A detailed process evaluation will run parallel to the trial, following the Medical Research (MRC) process evaluation framework for Complex Interventions which emphasises the importance of considering interactions between implementation, mechanisms, and context [93]. This will enable a rich understanding of participating families and key stakeholders’ acceptability and feasibility of the proposed evaluation measures, as well as capturing issues around the implementation of IPS as they unfold within the current context. Estimates of treatment effectiveness should not be the aim of feasibility trials [94], however, through a carefully conducted process evaluation we can track the ways in which IPS evolves and impacts as a service, capturing and exploring issues as they arise throughout the trial and feeding into service development. The process evaluation will be conducted at regular timepoints, capturing the early stages of IPS delivery and how it evolves as a new service from multi-perspectives (Fig. 4).

**Fig. 4 Fig4:**
[figure not shown]
Overview of the partnership for change study

#### Parents

Parents taking part in the study (IPS or SAU) will be invited to participate in up to two semi-structured interviews. The first interview will take place soon after baseline and will explore a sample (n6-8) of parent’s experience of, and access to mental health services and expectations of participating in the research. At follow up of 3-to-6 months, all parents will then be asked to take part in a second interview, centring around their engagement with the research process, including their experience and understanding of the randomisation and consent process, suitability of the assessments (including the PREM and PROMs), and practical aspects of participating in the research. Individual one-to-one interviews are the preferred method of data collection given the potential sensitivity of topics raised and the need for flexibility.

#### Parent Collaborators

The co-production values of equality, diversity, access, and reciprocity [65] run throughout all phases of the trial, ensuring that individuals who have been previously silenced by structural inequalities are able to have a voice and an equal role in shaping the IPS teams. Parent collaborators will continue to take an active role during the intervention roll out phase, providing advice and guidance on the conduct of the trial, such as resolving difficulties around recruitment and retention and engagement with IPS or the research process. Learning will be captured through meeting minutes and strategically placed focus groups or interviews, for example following the assessment phase of IPS to capture challenges, modifications, and improvements as the service evolves (Fig. 4).

#### IPS and Services as Usual Practitioners

Focus groups will be conducted with each of the teams delivering IPS and SAU across both sites, including Family Engagement Workers and Family Liaison Workers (the latter in Glasgow only) focusing on the perceived changes in the organisation, access, and quality of services. Practitioners will be encouraged to explore referral pathways into IPS or other services within SAU, the perceived acceptability of intervention components, including any drivers and barriers to successful implementation (from their own or the families’ perspective), how it fits within the local context, highlighting potential differences across settings, as well as perceptions around the research process itself. Focus groups are particularly useful for professional or other groups used to sharing experiences, allowing the group dynamic to facilitate the safe emergence of different perspectives [95].

#### Emergent Issues

Through an iterative process of data collection and analysis, any emergent issues or unforeseen difficulties that arise from the process evaluation will be explored further as the trial progresses. These findings may highlight the need to interview other professional groups or stakeholders who had not been formerly considered. Previous work has highlighted how qualitative approaches can be powerful in developing new and strengthening existing relationships across groups and agencies [96]. Utilising an iterative approach will be fundamental to identifying potential sites for a definitive RCT. Findings will be shared across parent collaborators and professional stakeholder groups to identify whether barriers and facilitators to services can be refined and developed into codesign responses.

### Participant Timeline {13}

Study procedures are summarised in Table 2.

### Sample Size {14}

We plan to recruit 30 families from Glasgow or London, with 15 families randomly allocated to IPS and 15 to SAU. Since the primary aim of this study is to assess recruitment rates, retention rates, and the acceptability of proposed measures, a formal power calculation is not appropriate. Our sample size was chosen to ensure a meaningful assessment of feasibility. If the true retention rate is 70%, the 90% confidence interval for this estimate will be approximately ± 15%, which we consider sufficiently precise for a feasibility study [97]. This level of precision allows us to make an informed decision about the feasibility of a larger trial. Additionally, as Hertzog (2008) [98] notes, the sample size for pilot studies should balance precision with logistical constraints, which we have considered in our planning. Furthermore, if the true retention rate is 70%, there is an > 80% probability that the observed retention rate will exceed 60%. If the observed retention rate falls below 60%, this would suggest that a future full-scale study is unlikely to be feasible without modifications. Even if feasibility is demonstrated, any future trial will include an internal pilot phase with close monitoring to ensure robust outcome data can be collected at scale.

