		• Numbers and percentage of families interested, assessed for eligibility, meeting the inclusion criteria and included, of the total number identified	≥ 15 participants recruited per site, total 30 participants	**Amber**: If recruitment is below 30 families, adjust recruitment strategies or explore alternative pathways
		• Qualitative data on recruitment procedures and pathways (through interviews with the recruitment co-ordinator and professionals)	No criteria set	**Amber:** If significant barriers are identified, revise recruitment strategies or consider new outreach methods
	Participant eligibility	• Qualitative data on ambiguities regarding eligibility criteria, reasons for ineligibility and reasons for non-participation (through interviews with the recruitment co-ordinator and professionals)	No criteria set	**Amber**: Revise eligibility criteria or adjust strategies if significant ambiguities or issues are identified
	Randomisation	• Numbers and percentage successfully randomised at each trial site (target n15 at each site)	≥ 15 participants recruited per site, total 30 participants	**Green**: No adjustment needed if the target recruitment of 15 participants per site is met **Amber**: If randomisation sucess is lower than expected, revise recruitment or randomisation procedures
		• Qualitative data on participant understanding and acceptability of recruitment/ randomisation processes	No criteria set	**Amber**: Revise randomisation procedures or provide additional clarification if acceptability or understanding is low
Retention and attrition rates	Retention	• Number and percentage of families retained in the study for 3-6 months post randomisation	70% of participants retained at 3-6 months	**Green:** No adjustment needed if retention is at or above 70% **Amber:** If retention falls below 70%, explore reasons for attrition and adjust strategies (e.g., follow-up support) **Red**: If retention falls below 50%, review follow-up methods and consider additional participant engagement strategies
	Attrition	• Qualitative data on reasons for attrition (through interviews with the recruitment co-ordinator and professionals and quantitative data collected via online data management system)	No criteria set	**Amber:** If attrition is high, explore the reasons for attrition and revise follow-up methods or engagement strategies accordingly

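### The sample size section reads retention against a 60% line that the progression criteria in Table 1 do not contain, so its >80% assurance does not describe the 70% rule that will be applied

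*Protocol article*

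**What the plan says.** Sample Size {14} sets the size of the study: "We plan to recruit 30 families from Glasgow or London, with 15 families randomly allocated to IPS and 15 to SAU". It gives two supports for that number. The first is precision: "If the true retention rate is 70%, the 90% confidence interval for this estimate will be approximately ± 15" percentage points. The second concerns a threshold. At the same true rate of 70%, "there is an > 80% probability that the observed retention rate will exceed 60" per cent. The section then gives that threshold a meaning: "If the observed retention rate falls below 60%, this would suggest that a future full-scale study is unlikely to be feasible without modifications".

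Table 1, under Objectives {7}, holds the progression and adaptation criteria. For retention the feasibility criterion is "70% of participants retained at 3-6 months". The three bands are:

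- Green: "No adjustment needed if retention is at or above 70" per cent.
- Amber: "If retention falls below 70%, explore reasons for attrition and adjust strategies".
- Red: "If retention falls below 50%, review follow-up methods and consider additional participant engagement strategies".

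The table's footnote defines Green as no change, Amber as minor change and Red as major change. The figure of 60% appears nowhere in the table, and the sample size section does not mention the colour bands.

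**The concern.** Retention is one of the two elements of the primary outcome, and the Discussion bases progression to a full trial on recruitment and retention. The article gives two cuts for this one observed percentage and does not say how they relate. Table 1 calls for adjustment once retention drops below 70%. Sample Size {14} places its warning that modifications are needed at 60%.

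Two things follow. First, the only threshold probability offered in support of 30 families belongs to a line that the progression table does not use. A reader could take it as the chance that a trial retaining families at the assumed rate meets the feasibility criterion, and that chance is much lower. Second, a result in the 60s can be described in two ways, and the choice between descriptions would be made after the result is known unless the text settles it beforehand.

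**Working it through.** **Inputs**

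- n = 30 families randomised (Sample Size {14}).
- Denominator: all participants randomised (Statistical Methods {20A}).
- Assumed true retention p = 0.70 (Sample Size {14}).
- Line in Sample Size {14}: 60%, which is 18 of 30. Exceeding it means at least 19. Falling below it means at most 17.
- Bands in Table 1: Green at least 70%, so at least 21 of 30. Red below 50%, so at most 14. Amber is what lies between, 15 to 20.

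**Formula**

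With X the number of families retained, X ~ Binomial(30, p) and P(X ≥ r) = Σ from k = r to 30 of C(30, k) p^k (1 − p)^(30 − k).

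**Step 1: reproduce the article's own figures (p = 0.70)**

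- Probability of exceeding 60%: P(X ≥ 19) = 0.841. The normal approximation gives 0.884, or 0.840 with continuity correction. All are above 80%, so the statement is correct. Counting exactly 60% as well, P(X ≥ 18) = 0.916.
- Half-width of the 90% interval: 1.645 × √(0.7 × 0.3 / 30) = 1.645 × 0.0837 = 0.138, or 13.8 points. This agrees with the rounded 15.

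**Step 2: the Table 1 rule at the same true rate**

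- Green: P(X ≥ 21) = 0.589.
- Amber: P(15 ≤ X ≤ 20) = 0.9936 − 0.5888 = 0.405.
- Red: P(X ≤ 14) = 1 − 0.9936 = 0.006.

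A trial whose true retention equals the criterion therefore misses Green with probability 1 − 0.589 = 0.411.

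**Step 3: split Amber at the 60% line (p = 0.70)**

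- 18 to 20 of 30 (60% to 67%): 0.9155 − 0.5888 = 0.327. Not below the 60% line, but short of the 70% criterion.
- 15 to 17 of 30 (50% to 57%): 0.9936 − 0.9155 = 0.078. Below the 60% line, and Amber in Table 1.

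**Step 4: other true rates**

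| True retention | P(observed > 60%) | Green | Amber | Red |
|---|---|---|---|---|
| 60% | 0.431 | 0.176 | 0.727 | 0.097 |
| 65% | 0.655 | 0.358 | 0.612 | 0.030 |
| 70% | 0.841 | 0.589 | 0.405 | 0.006 |
| 75% | 0.949 | 0.803 | 0.196 | 0.001 |

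Amber is one minus Green minus Red. Green reaches 80% only when true retention is about 75%.

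**The case against.** The best defence is that Sample Size {14} makes no false statement. It names its event, and the probability for that event is right. Only Table 1 is labelled as progression criteria, the 60% sentence is worded as a suggestion, and the leading support for 30 families is the width of the confidence interval, which is unaffected. A cut placed at the assumed true rate will always be met only somewhat more than half the time at this sample size, so 59% is a property of the rule and not a mistake. The study is also standalone and does not lead directly into a larger trial.

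Most of that stands, and it rules out several stronger readings:

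- A reader might infer that the >80% is miscalculated. It is not.
- A reader might infer a flat contradiction at 50% to 59%. Both places call for changes there, and the 60% sentence does not say whether those changes are minor or major.
- A reader might infer that Sample Size {14} passes a result of 60% to 69%. It says only what a result below 60% would suggest and gives no verdict at or above that line.
- A reader might infer that the Red line at 50% is too low. Nothing in the article makes 50% wrong, and moving it would be a design preference. At a true rate of 50%, Green has probability only 0.021, so almost every such trial would still trigger Amber or Red action.

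What the defence does not supply is a role for 60%. Either the figure triggers something that Table 1 omits, or it triggers nothing and the quoted assurance concerns a boundary without consequence. On neither reading does >80% describe the 70% criterion. Leaving detail to a fuller protocol or analysis plan does not answer this, because both cuts are printed in this article.

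**Conclusion.** The point holds as an internal inconsistency. One element of the primary outcome has two stated cuts, 60% in Sample Size {14} and 70% in Table 1, with no link between them, and the assurance supporting the sample size is quoted for the cut that the progression table does not use. At a true rate of 70%, the stated figure corresponds to 0.841, whereas the Table 1 criterion is met with probability 0.589. The band that sits differently against the two cuts, 18 to 20 of 30, has probability 0.327.

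These probabilities assume that all 30 families are randomised and that families are retained independently at a common rate. The mismatch between the two sections is textual and does not depend on those assumptions. Neither the precision argument for 30 families nor the planned descriptive analysis is affected.

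**What to change.** Use one set of retention cuts in both places. The simplest route is to leave Table 1 as it is and edit Sample Size {14}:

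1. Remove the two sentences built on 60%, or add a sentence saying how 60% relates to the bands, for example whether it is a marker within Amber and what follows from crossing it.
2. Replace the >80% figure with the properties of the Table 1 rule at a true 70%: 59% Green, 40% Amber and under 1% Red, assuming 30 families randomised and independent retention. It would help to add that Green reaches 80% at a true rate of about 75%.

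This should be settled before retention is read. The cost is a few sentences, with no extra families and no change to procedures or analysis. The downside is that the quoted assurance becomes less favourable.
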